## Abstract

**Background:**

Individuals with severe chronic obstructive pulmonary disease (COPD) are often at risk of undernutrition with low health-related quality of life (HRQoL). Undernutrition can worsen COPD and other comorbidities, be an independent predictor of morbidity and functional decline resulting in increased healthcare consumption and increased risk of death. Especially exacerbations and acute infections result in unintentional weight loss. The aim is to investigate the effect of an individualized nutritional intervention among individuals with severe COPD.

**Methods:**

An open-label randomized controlled trial with two parallel groups. Participants are recruited from the pulmonary outpatient clinic at the Department of Pulmonary and Infectious Diseases, Copenhagen University Hospital, North Zealand, Denmark, and randomly allocated to either the intervention (intervention + standard of care) or control group (standard of care). The intervention has a duration of 3 months and combines individual nutritional care with adherence support and practical tools. It contains 4 elements including an individual nutritional plan, regular contacts, adherence support, and weight diary. The primary outcome is a difference in HRQoL (EQ-5D-5L) between the intervention and control group 3 months after baseline. Difference in functional capacity (grip strength, 30-s stand chair test, and physical activity), disease-specific quality of life (COPD Assessment Test), anxiety and depression (Hospital Anxiety and Depression Scale), nutritional parameters (energy and protein intake), anthropometry (weight, body mass index, waist, hip, and upper arm circumference), body composition (total fat-free and fat mass and indices), and prognosis (exacerbations, oxygen therapy, hospital contacts, and mortality) 3 months after baseline will be included as secondary outcomes. Data will be collected through home visits at baseline and 1 and 3 months after baseline.

**Discussion:**

Currently, nutritional care is a neglected area of outpatient care among individuals with severe COPD. If this patient-centered approach can demonstrate a positive impact on HRQoL, mortality, and hospital contacts, it should be recommended as part of end-of-life care for individuals with severe COPD.

**Trial registration:**

ClinicalTrials.gov NCT04873856
. Registered on May 3, 2021.

Role of sponsor {5c}	The sponsor is involved in study design, data collection, data management, data analysis, interpretation of the results and in deciding which journals manuscripts will be submitted to. The funder will have no role in study design, data collection, data management, data analysis, interpretation of the results and in deciding which journals manuscripts will be submitted to

## Introduction

### Background and rationale {6a}

Chronic obstructive pulmonary disease (COPD) is a frequent chronic disease and a serious global health concern that imposes significant burdens for individuals and societies. In Denmark, an estimated number of 50,000 individuals are living with severe COPD [1], and COPD is the third leading cause of death with the highest mortality rate in the European Union [2]. Each year, 25,000 hospitalizations have COPD as the primary diagnosis, and hospitalization due to COPD is related to a high risk of mortality with 7% dying within a hospital and 25% within the first year after discharge [1]. Severe COPD is associated with a high symptom burden, increased risk of anxiety, and depression, all with a negative impact on health-related quality of life (HRQoL) [3].

COPD is also closely linked to undernutrition, a state of malnutrition in which the intake of energy and protein falls below the biological needs, and in individuals with severe COPD, undernutrition is likely caused by several factors including metabolic and pathophysiological changes as well as social and mental conditions [4]. Undernutrition can worsen COPD and lead to increased morbidity and functional decline resulting in increased healthcare consumption and risk of death [4]. Inadequate dietary intake is common among individuals with COPD [5]. Especially pulmonary exacerbations and acute infections result in unintentional weight loss [6]. Undernutrition is associated with decreased HRQoL [7], low physical capacity [8], and mortality [9].

Comorbidities such as anxiety and depression are common but have frequently been overlooked because the symptoms overlap the symptoms related to COPD itself. Without recognition and medical treatment, depression and anxiety symptoms may have serious negative effects on HRQoL, functional capacity, and social interaction as well as increasing fatigue, more frequent exacerbations, and hospitalizations [10, 11].

Systematic reviews have suggested that nutritional support in COPD improves nutritional intake, anthropometric measures, functional capacity, and HRQoL. Many of the studies included in these reviews are conducted more than 30 years ago and based on small sample sizes. In addition, the interventions were not individualized, only a few studies focus on outpatients exclusively with severe COPD, and prognostic outcomes such as hospitalizations and mortality are very sparse [12, 13]. Nutritional care is an important but neglected area in the care of COPD likely due to knowledge gaps and the absence of professional responsibility [14]. There is a need for developing strategies to handle this underprioritized and complex problem in severe COPD. This paper describes a study protocol for a registry-based randomized controlled superiority trial investigating the effect of an intervention combining nutritional care with socio-emotional and adherence support and practical tools for improving HRQoL as well as nutritional status and prognosis in individuals with severe COPD.

### Objectives {7}

The objective is to investigate the effectiveness of multidimensional individualized nutritional therapy with a duration of 3 months on HRQoL as well as several clinical outcomes.

Primary outcome:HRQoL

Secondary outcomes:2)Hospital contacts3)Mortality4)Disease-specific quality of life5)Anxiety and depression6)Functional capacity7)Anthropometry8)Body composition9)Exacerbations10)Physical activity11)Energy and protein intake12)Difference between protein and energy requirement and intake

### Trial design {8}

The study is a single-center, home-based, effectiveness, registry-based randomized controlled superiority trial with two parallel groups.

## Methods: participants, interventions, and outcomes

### Study setting {9}

The recruitment takes place at the Department of Pulmonary and Infectious Diseases, Copenhagen University Hospital, North Zealand, Denmark. All data collection is carried out through home visits, telephone calls or medical records.

### Eligibility criteria {10}

When potential participants are identified, the study coordinator will screen them for eligibility.

Inclusion criteria ≥ 35 yearsSevere COPD defined as GOLD grade 2 group B or D OR GOLD grade 3 and 4 group ABCD [15]Able to eat orallyLive in own homeSpeak Danish or EnglishUndernourished (BMI < 18.5 kg/m.^2^) OR at risk of undernutrition (a maximum BMI of 25 kg/m2) determined by Nutritional Risk Screening 2002 (NRS2002) or Mini Nutritional Assessment short form (MNA-SF)Stable phase

Exclusion criteria“Active solid cancer” defined as cancer diagnosed within the previous 6 months, recurrent, regionally advanced, or metastatic cancer, cancer for which treatment had been administered within 6 months or hematological cancer that is not in complete remission [16].Unable to sign informed consent, e.g., due to severe dementia.Severe chronic renal failure defined as estimated glomerular filtration rate < 30 mL/min./1.73 m^2^ (ICD-10 codes N18.4 and N18.5).Severe alcohol abuse (ICD-10 codes F10.2 and K70.x).

Drop out criteria.

Lost to follow-upWithdrawal

### Daily management

All contact with the participants will be coordinated and conducted by the study coordinator.

### Who will take informed consent? {26a}

The written informed consent will be obtained at the first home visit prior to baseline data collection by the study coordinator.

### Additional consent provisions for collection and use of participant data and biological specimens {26b}

Participants are informed that signing the informed consent gives the researchers permission to save and store their personal information and data for future research on the effect of multidimensional individualized nutritional therapy. This study does not involve collection of biological material.

## Interventions

### Explanation for the choice of comparators {6b}

Standard of care augmented with a multidimensional individualized nutritional therapy will be compared to the standard of care. It is the intention that this study will highlight the importance of enhancing the focus of HRQoL, nutritional, socio-emotional, and adherence support compared to the current standard of care.

### Intervention description {11a}

#### Public and patient involvement

There was no public or patient involvement in the design of this protocol.

#### Nutritionally augmented standard of care

The intervention has been designed by a multidisciplinary team of experts within pulmonary medicine, infections, nutrition, and physical (in)activity. The intervention has a duration of 12 weeks. In addition to standard of care, the intervention contains four elements including (1) individual nutritional plan, (2) regular contact, (3) adherence support, and (4) weight diary. The four elements are described below:*Nutritional plan* is developed and adjusted with the participant based on nutritional registration, information about routines and habits and nutritional preferences to reach a daily protein target of 1.5 g protein/kg/day [17] and individual energy requirements of 30–45 kcal/kg/day [17]. The nutritional plan is adjusted at the regular contacts. The nutritional plan may include supplementation with energy and protein-rich products and during the intervention period, a document summarizing tools and advices are provided.*Regular contacts* are phone calls from the project coordinator every 7–14th day to talk about the nutritional plan, well-being, adherence, or potential side effects.*Adherence support* is provided through the regular contact and a friendly reminder that encourages the participant to follow the nutritional plan and to ask for support (a note to hang on the refrigerator).*Weight diary* is a daily registration of weight.

Note: It is likely that participants in both groups will be hospitalized during the intervention period. As far as possible the study coordinator will continue the intervention during hospitalization. Hospitalizations with acute infections such as pneumonia and exacerbation are common among individuals with severe COPD and both conditions increase nutritional requirements. It is therefore essential to maintain the contact with nutritional and mental support during hospitalization.

### Standard of care

At the Department of Pulmonary and Infectious Diseases at Copenhagen University Hospital, North Zealand, each patient is assigned with a nurse and offered an annual conversation about advance care planning. The purpose of advance care planning is to talk about disease severity, prognosis, treatment options, symptom burden, and preparation for the late stages and death. The nurses have the responsibility to maintain a personal relationship and are available by phone every working day with the possibility to get an appointment within 2 working days. A rehabilitation program combining physical training and education on all aspects of COPD is offered every second to third year, though the rehabilitation program has a very limited focus on nutrition.

### Criteria for discontinuing or modifying allocated interventions {11b}

The risk of side effects related to intake of nutritional supplementation is considered minimal and potential side effects is expected to be mild, primarily in the form of gastrointestinal symptoms. There are no known long-term risks.

### Strategies to improve adherence to interventions {11c}

The strategies to improve adherence to the intervention are integrated in the design in different ways. First, the adherence support and the regular contacts encourage the participant to follow the nutritional plan and remind the participant of the opportunity to ask for help and support. The regular contact also allows for adjusting the plan to improve adherence if the participant experience challenges in reaching the nutritional targets as the nutritional intake will be registered regularly during the intervention period. In addition, this conversation is also an opportunity for the participant to talk about well-being, potential side-effect or other challenges or issues or topics of interest.

### Relevant concomitant care permitted or prohibited during the trial {11d}

The participants can receive all forms of care. We encourage to act and live as normal as possible during this trial. Contact with the outpatient clinic and the hospital will be registered.

### Provisions for post-trial care {30}

The participants will not receive any post trial care beyond standard of care.

### Outcomes {12}

#### Primary outcome

The primary outcome is HRQoL measured using the EuroQoL EQ-5D-5L questionnaire [18], a generic health status questionnaire that has been validated in individuals with COPD [19].

#### Secondary outcomes

Secondary outcomes are weight and BMI, total fat-free mass, fat mass, and indices measured 3 months after baseline. Disease-specific quality of life measured as mean total score 1 and 3 months after baseline. Functional capacity measured as grip strength [20] and the 30-s chair stand test measured 1 and 3 months after baseline [21]. Hospital contact (outpatient contact by phone or visits, unplanned acute visit to the emergency ward (< 6 h), and unplanned acute hospital admission) is measured as the number of contacts between baseline 1 and 3 months after baseline. In addition, hospital admissions will also be measured as total days spent in the hospital during the 3-month study period. Mortality will be measured as percentage of individuals who died between baseline and end of the study period (3 months after baseline).

#### Other outcomes

Other outcomes are waist, hip, and upper arm circumference. Exacerbations are measured as the number of exacerbations between baseline and 3 months after baseline. Oxygen therapy is measured as percentage using home oxygen 3 months after baseline. Anxiety and depression as percentage of individuals with symptoms of any of the two conditions. Physical activity level is assessed with a questionnaire and with accelerometers 7 days from baseline and 7 days from the 3-month follow-up visit. Total protein and energy intake will be used as nutritional outcomes. In addition, for energy and protein, the difference between intake and requirement will be another outcome. Requirements are defined as follows: The protein target for all participants is defined as 1.5 g protein/kg/day [17], whereas energy requirements will be individually evaluated according to age and BMI. The energy requirements will be defined as 30 kcal/kg/day for weight maintenance and 45 kcal/kg/day for weight gain [17]. For participants < 70 years with BMI < 20 kg/m^2^ and participants ≥ 70 years with BMI < 22 kg/m^2^ the goal is weight gain [22], whereas the goal is weight maintenance for the remaining participants.

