**Secondary outcomes**							
Hospitalizations	Acute hospitalizations (all causes)		x	x		x	Numerical
Days in hospital	Number of days in hospital (all causes)		x	x	x		Numerical
Other hospital contacts	Acute hospital contacts < 6 h		x	x	x		Numerical
Contact to the outpatient clinic	Contact to the outpatient clinic via phone or visit		x	x	x		Numerical
Mortality	Mortality (number of deaths)		x	x		x	Binomial
Disease-specific quality of life	COPD Assessment Test	x	x	x	x		Numerical
Anxiety and depression	Hospital Acquired Depression Scale	x	x	x		x	Binomial
Muscle strength	Grip strength	x	x	x	x		Numerical
Muscle endurance	30-s chair stand test	x	x	x	x		Numerical
Fat-free mass	Bioelectrical impedance analysis	x	x	x	x		Numerical
Fat mass	Bioelectrical impedance analysis	x	x	x	x		Numerical
Weight	Electronic scale	x	x	x	x		Numerical
Body mass index	Weight (kg)/height(m^2^)	x	x	x	x	x	Numerical/categorical

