#### Depression and anxiety

The risk of depression and anxiety will be determined using Hospital Acquired Depression Scale (HADS). HADS contains two subscales to evaluate the risk of anxiety and depression. Each subscale contains 7 items with a total score from 0–21. Risks of anxiety and depression are based on a total score ≥ 8 and a total depression score ≥ 8 or ≥ 5 (if the scale is reduced with one item), respectively [30].

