## Statistical methods

### Statistical methods for primary and secondary outcomes {20a}

#### Main analysis

Data on the primary outcome as well as all continuous secondary and other outcomes will be analyzed using linear mixed models that include an intervention group-time interaction as a fixed-effects term whereas between-participant variation is captured by means of (participant-specific) random (intercept) effects. There will also be random effects for the blocks used to account for the block randomization [42]. Baseline values will be part of the outcome [43].

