#### Sensitivity analysis

Additionally, linear mixed models that also include relevant covariates (as fixed effects) will be fitted to adjust for observed baseline imbalance (if needed). Relevant covariates include age, BMI, sex, pulmonary function, and the number of comorbidities.

For all fitted linear mixed models, the two estimated mean changes from baseline to 3 months (for both intervention groups) as well as the estimated mean difference in change from baseline to 3 months will be reported together with the corresponding 95% confidence intervals and *p* values. Statistical significance will be declared whenever the *p*-value is below 0.05.

Where appropriate, outcome values will be transformed prior to the statistical analysis.

For categorical secondary or other outcomes data will be analyzed by means of logistic mixed-effects regression models that include an intervention group-time interaction as a fixed-effects term and block and participant-specific random effects. Baseline values will be part of the outcome. The estimated difference in change from baseline to 3 months will be reported as a ratio of odds ratios together with the corresponding 95% confidence interval and *p* value.

Statistical analyses will be carried out using STATA/IC version 17.0 (StataCorp LP, USA). Specifically, the commands XTMIXED and XTMELOGIT will be used for fitting linear mixed models (using residual maximum likelihood estimation) and logistic mixed-effects regression models (using maximum likelihood estimation), respectively.

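### HADS is analysed only as a percentage above a cut-off, although two 0–21 scores are collected at every visit and the plan already has a model for scores

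*Protocol article*

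**What the plan says.** All references are to the protocol article.

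- **Definition.** Outcomes {12}, Other outcomes: "Anxiety and depression as percentage of individuals with symptoms of any of the two conditions".
- **Variable type.** Table 2 lists the instrument (there named "Hospital Acquired Depression Scale") at baseline, 1 month and 3 months. It is marked under percent/proportion, not mean/median, and typed binomial.
- **Scores collected.** Depression and anxiety: "Each subscale contains 7 items with a total score from 0–21".
- **Cut-offs.** The same section bases the two risks on "a total score ≥ 8 and a total depression score ≥ 8 or ≥ 5 (if the scale is reduced with one item), respectively".
- **Model for this outcome.** Statistical methods {20a}: "For categorical secondary or other outcomes data will be analyzed by means of logistic mixed-effects regression models", and "The estimated difference in change from baseline to 3 months will be reported as a ratio of odds ratios".
- **Model for scores.** Main analysis: "all continuous secondary and other outcomes will be analyzed using linear mixed models". In Table 2 the EQ-5D-5L, CAT and Physical Activity Vital Sign are all numerical. The CAT is reported as a mean total score, although the article also gives severity bands for it.
- **Tier.** The Abstract, Objectives {7} and Table 2 make anxiety and depression secondary. The text of Outcomes {12} puts them under other outcomes.

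No section plans an analysis of either HADS score.

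**The concern.** The yes/no version ignores all movement that does not cross the cut. A participant whose anxiety score falls from 16 to 9 stays at or above 8 and counts as unchanged. If the definition means one merged outcome, a participant whose depression resolves while anxiety persists also counts as unchanged.

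The Background and the Discussion give anxiety and depression a prominent place, and the Discussion puts mental health beside HRQoL among the outcomes that matter most to patients at the end stage. An insensitive measure makes a null result here hard to read: it could reflect no effect, or an effect that the cut did not register.

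The article gives no reason for treating HADS differently from the other questionnaires. It also leaves open which depression cut-off defines the outcome, because it does not say whether the full or the shortened scale is used.

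**Working it through.** **1. The plan's own figure.** There is none for HADS. The only size calculation is for the primary outcome (Sample size {14}: difference 10, SD 17, power 0.8, significance level 0.05 taken as two-sided, drop-out 20%). It reproduces: 2 × (1.960 + 0.842)² × 17² / 10² = 45.4, so 46 per arm; 46 / 0.8 = 57.5, so 58, against the stated 60. After 20% drop-out, 60 per arm leaves 48, or 96 in all. The 96 is used below.

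**2. One score cut once.** Assume a roughly normal score with a fraction p above the cut. For a small shift, the information kept by the yes/no version relative to the score is φ(z)² / [p(1 − p)], where z is the normal quantile for p and φ is the normal density. The article gives no p, so a range is shown.

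| Assumed p | Information kept | Lost | 96 participants are worth about |
|---|---|---|---|
| 50% | 0.399² / 0.25 = 0.64 | 36% | 61 |
| 40% or 60% | 0.62 | 38% | 60 |
| 30% or 70% | 0.348² / 0.21 = 0.58 | 42% | 55 |
| 20% or 80% | 0.280² / 0.16 = 0.49 | 51% | 47 |

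Below 20% or above 80% the loss is larger (66% at 10%). Replacing the normal by a beta-binomial 0–21 score cut at 8, with assumed mean 5–8 and SD 3.5–4, gives 35–47%. The result therefore does not hinge on normality.

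**3. The either-condition composite.** Assume two normal subscales with correlation ρ and the same cut c on each. If both shift equally, the composite proportion changes at rate 2φ(c)Φ[c(1 − ρ)/√(1 − ρ²)]. If only one shifts, the rate is half of that.

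Example with ρ = 0.5 and 30% above each cut (c = 0.524):

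- The composite prevalence is 0.443, with variance 0.443 × 0.557 = 0.247.
- Both shift: rate 2 × 0.348 × 0.619 = 0.430; 0.430² / 0.247 = 0.75. The loss against one subscale score is 25%.
- Both shift, compared with the total of the two scores, whose information is 4 / (2 + 2ρ) = 1.33: 0.75 / 1.33 = 0.56, a loss of 44%.
- One shifts: rate 0.215; 0.215² / 0.247 = 0.19. The loss against that subscale's score is 81%.

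Over assumed ρ = 0.4–0.7 and 15–40% above each cut, the three losses are 22–44%, 40–54% and 80–86%.

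**4. Illustrative power.** Assume a 0.5 SD shift and 48 per arm, compared at one time point. For the score: Φ(0.5 × √24 − 1.96) = 0.69. For the yes/no version (two-proportion z-test), with the treated proportion equal to Φ[Φ⁻¹(p) − 0.5]:

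| Control | Treated | Power |
|---|---|---|
| 50% | 30.9% | 0.48 |
| 30% | 15.3% | 0.41 |
| 20% | 9.0% | 0.33 |

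The 0.5 SD has no source in the article and serves only to show the scale.

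**The case against.** The sections on HADS agree with one another about what is measured and how. A percentage above a cut-off is a pre-specified choice that clinicians read easily, so this is not an error or a contradiction. That stands: the point is about an avoidable loss of sensitivity. It is equally not a gap that an unseen analysis plan might fill, since variable type, summary and model are all stated.

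Four stronger readings are tempting, and the document does not support them.

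- **That a fixed share of the information is thrown away.** The article gives no HADS prevalence, SD, subscale correlation or expected effect. The 36–51% belongs to one cut score at an assumed prevalence. The composite can lose less (22–44% against one subscale) or far more.
- **That the two conditions are certainly merged.** The definition could also mean one percentage per condition, since the section on depression and anxiety sets a cut-off for each. On that reading the masking of one condition by the other falls away, and only the cut remains.
- **That few participants will change status.** No transition rate is given.
- **That two competing depression cut-offs are in force.** The lower one is tied to a shortened scale ("if the scale is reduced with one item"). What is missing is a statement of which version is used, and that is a smaller clarification.

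The odds-ratio summary is likewise no special fault of HADS; it applies to every categorical outcome in the plan.

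**Conclusion.** The concern holds as a worthwhile improvement to a non-primary outcome. The plan fixes HADS as a yes/no percentage, although two scores are collected at all three visits and a suitable model is already specified. No reason is given for departing from the practice used for the other questionnaires.

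For a single roughly normal score with an assumed 20–80% above the cut, the loss is about 36–51%. For a merged outcome the size depends on the subscale correlation and on whether one or both subscales respond, so no single figure should be attached to it. The masking argument applies only under the merged reading.

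The primary analysis and the sample size are untouched. How much weight the outcome carries is itself unsettled, because the article places it in two different tiers.

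**What to change.** In a dated, documented change made before outcome data are examined by arm:

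- Analyse the HADS anxiety score and the HADS depression score separately, each with the linear mixed model of the Main analysis.
- Keep the percentage above the cut-off as a supportive or descriptive result, for each subscale separately.
- State which version of the depression scale is used and the cut-off that goes with it.
- Reconcile the outcome tier between the text of Outcomes {12} and the Abstract, Objectives {7} and Table 2.

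**Cost.** No new data, visits or participants are needed. There would be two results instead of one. At an unadjusted 0.05 each, the chance of at least one false positive is at most 0.05 + 0.05 = 0.10, so both should be reported together. A score difference is less immediate clinically than a percentage, which is why the percentages are kept. The change alters a pre-specified outcome in an open-label trial that has enrolled since May 2021 and whose coordinator delivers the intervention, collects the data and analyses them. The date and the blinded state at the time of the change should therefore be on record.
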